#### Sample size justification

2.2.4

Power calculations for the primary cross-sectional study were informed by previous investigations of cortical hyperexcitability and subclinical epileptiform activity (SEA) in neurocognitive disorders [summarized by Horvath et al. (2020)]. Assuming a medium effect size (Cohen’s *d* = 0.5), a two-sided significance level of α = 0.05, and four diagnostic groups, a sample size of 75 participants per group (total *N* = 300) provides more than 90% power to detect clinically meaningful between-group differences in the primary outcomes, including the incidence of SEA and resting-state fMRI hyperactivity.

The mechanistic in-ward substudy is enrichment-based and will include participants demonstrating evidence of cortical hyperexcitability. Assuming a conservative prevalence of approximately 15% across the clinical groups, we anticipate recruiting approximately 45 eligible participants, with an expected final sample of approximately 40 after accounting for an estimated 20% attrition rate.

The mechanistic substudy is designed primarily to characterize within-subject physiological relationships among cortical hyperexcitability, sleep architecture, memory consolidation, and circulating biomarkers using repeated-measures analyses. Because repeated observations substantially increase statistical efficiency for within-subject comparisons, this sample size is considered appropriate for estimating effect sizes, assessing feasibility, and identifying candidate mechanistic pathways. In contrast, more analytically demanding models, including formal mediation analyses and subgroup comparisons across diagnostic categories, are expected to have limited statistical power with the anticipated sample size. Accordingly, these analyses will be considered exploratory and hypothesis-generating, with emphasis placed on effect size estimation, confidence intervals, and model uncertainty rather than statistical significance alone. Findings from these exploratory analyses will inform sample size calculations and analytic strategies for future confirmatory multicenter studies.

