#### Resting-state fMRI

2.3.3

Resting-state fMRI will be acquired using T2*-weighted echo-planar imaging (EPI) sequences (TR 2,000 ms; TE 30 ms; flip angle 70–79°; voxel 3 × 3 × 3–4 mm; ∼10-min duration). Participants will be instructed to remain still, keep their eyes closed (or fixate on a cross, as per the scanner-specific protocol), and avoid falling asleep.

Preprocessing and functional connectivity analysis will be performed with the CONN toolbox (MATLAB) using a standard pipeline:

Realignment and unwarping; slice-timing correction.Outlier detection (ART-based scrubbing).Direct segmentation and normalization (GM/WM/CSF, MNI space).Spatial smoothing.Band-pass filtering (0.008–0.09 Hz).Regression of white matter, CSF, and motion parameters.

Regions of interest (ROIs) will be defined *a priori* within the DMN, SN, and AN based on the literature and group consensus. Seed-based connectivity (SBC) analyses will compute Fisher-z-transformed correlations between ROI time series and voxel-wise signals. Age and sex will be included as covariates. Group differences (e.g., HC > MCI, HC > ASD, HC > ADHD) will be evaluated using voxel-wise ANCOVA with cluster-level FDR correction (cluster pFDR < 0.05; voxel *p* < 0.001 uncorrected). Hyperactivity will be defined as significantly elevated connectivity or activity within predefined network ROIs of DMN, SN, and AN relative to HC normative values obtained from our reference database (ACOL). For further details, see section “2.4.1 Participant selection and extraction of normative values.” Participants will be categorized as fMRI-positive or fMRI-negative for cortical hyperexcitability. The exact fMRI pipeline is characterized in previous studies published by our group (Bolla et al., 2023, 2025).

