All recordings will be independently reviewed by two experienced clinical neurophysiologists who are blinded to diagnosis and other clinical information. Epileptiform discharges will be accepted only when both reviewers reach consensus. Prior to consensus adjudication, inter-rater agreement will be quantified using Cohen’s κ coefficient for the presence or absence of subclinical epileptiform activity, with κ values and 95% confidence intervals reported in the final study results. Discordant cases will be reviewed jointly to establish the final classification. Automated spike detection (Persyst) will serve as a supporting tool for quantifying spike density, amplitude, and duration, while all final classifications remain based on expert visual assessment. The average spike density (spikes/hour) will be computed, and scalp distribution will be categorized (frontal, temporal, parietal, occipital, etc.) using Micromed SystemPLUS 98. Participants will be labeled as EEG-positive or negative for SEA relative to HC normative values obtained from our reference database (ACOL). The SEA detection pipeline is reported in our previous publications (Horváth et al., 2018b; Horvath et al., 2021).

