#### Participant selection and extraction of normative values

2.4.1

Across all groups (HC, MCI, ASD, ADHD), participants with clear evidence of cortical hyperexcitability—defined by at least one of: SEA on EEG above a predefined density threshold; or fMRI-defined hyperactivity in DMN/SN/AN—are invited to participate. We will initially prioritize HC and MCI subjects during the pilot phase to refine the in-ward protocol, then extend to ASD/ADHD.

Normative values for the fMRI and EEG metrics will be calculated using the ACOL dataset. The ACOL dataset is our clinical registry, founded in 2014, and contains longitudinal data from 500 individuals at various stages of the cognitive continuum. The dataset includes 280 healthy individuals (mean age = 55) with records on clinical anamnesis, demographics, blood-based biomarkers, neurological examination, medications, neuropsychology, 24-h Holter-EEG, 10-min resting EEG, sMRI, 10-min resting fMRI, pupillometric data, fine-movement analysis, and autonomic functions. All participants have been scanned with the same MRI scanner (Siemens Magnetom 3T) and examined with the same EEG recording system (Micromed Morpheus Holter-EEG). Further details on the dataset can be found at the EuroFingers Consortium website^1^.

To generate normative fMRI values, we perform rigorous preprocessing of all scans—motion correction, spatial normalization, smoothing, and signal denoising—to ensure comparability across individuals. Next, functional metrics, including functional connectivity strength, regional homogeneity (ReHo), amplitude of low-frequency fluctuations (ALFF), Hurst-exponent, and network efficiency, are extracted for each subject. Within the healthy control group, these measures are then aggregated and standardized by computing the mean and standard deviation of each metric across all participants to generate z-score distributions that define the “normal” range. Statistical modeling (Gaussian mixture) is used to identify normative intervals and detect outliers. To account for biological variability, the dataset is stratified by relevant covariates such as age, sex, and head motion. The resulting normative models can then serve as a statistical reference framework, allowing patient metrics to be expressed as deviation scores (z-scores) that quantify brain abnormalities relative to typical controls.

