To generate normative EEG values, we perform meticulous EEG preprocessing on 24-h recordings—artifact removal (e.g., eye blinks, muscle noise), filtering, and referencing—to ensure clean data. Two manual expert reviews of the files to identify potential SEA in line with the previously published protocols (Kamondi et al., 2024; Port et al., 2019). To define normal limits, the density, amplitude, duration, and spatial distribution of these events can be quantified across all control recordings. Statistically, normal values are represented by upper tolerance limits (the 95th percentile) of spike density (events per hour) computed from the control group. Normative modeling is applied to further refine these thresholds by accounting for age, sex, sleep state, and recording montage, variables known to influence EEG background and transient patterns. Additionally, spectral power and band ratios (delta, theta, alpha, beta, gamma) are used to construct normative baselines, against which epileptiform spikes produce transient deviations.

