#### Cross-sectional analyses

2.6.1

Data from all diagnostic groups will be pooled into a single multivariate dataset and analyzed using machine learning and dimensional reduction techniques to extract cross-diagnostic patterns of neural and behavioral variance. The model will test for latent factors reflecting shared E/I imbalance across disorders, while *post hoc* analyses identify disorder-specific deviations. Statistical adjustments will account for confounders such as age, medication, and cognitive status.

Primary outcome will be the (Torenvliet et al., 2023) incidence and distribution of SEA, and fMRI hyperactivity in each diagnostic group relative to controls. Secondary outcomes will include relationships between hyperexcitability and (a) structural atrophy and white matter integrity; (b) functional connectivity within and between default mode, salience, and attention networks; (c) CSF and plasma tau/Aβ levels; and (d) domain-specific cognitive performance.

Incidence of hyperexcitability (primary outcome):○Logistic regression models comparing SEA and fMRI-positive status between groups (MCI, ASD, ADHD vs HC), adjusting for age, sex, education, and disease duration where applicable.○Results will be reported as odds ratios with 95% confidence intervals.

Associations with cognition, structure, and connectivity (secondary outcomes):○Within each group, participants will be classified as hyperexcitability-positive vs negative (see section “2.4.1 Participant selection and extraction of normative values”).○For continuous outcomes (neuropsychological scores, cortical thickness/volume, DTI measures, functional connectivity indices, blood-based biomarker concentrations), group comparisons will use *t*-tests or Mann–Whitney U tests depending on normality (Shapiro-Wilk).○For categorical variables, chi-square tests will be used.○Multivariable linear models with covariates (age, sex, education, disease duration, mood/anxiety scores) will assess independent associations.Holm–Bonferroni corrections will be used to control for multiple comparisons.

Cross-modal relationships:○Correlation and regression analyses will examine relationships between spike density and fMRI hyperactivity.○Multimodal latent variable models or clustering approaches will be applied exploratorily to define hyperexcitability phenotypes.

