#### Biomarker development and validation

3.3.1

The multimodal dataset will allow derivation of a candidate biomarker panel of cortical hyperexcitability, combining:

SEA incidence, density, and spatial distribution from 24-h and video-EEG recordingsfMRI-based hyperactivity indices and aberrant connectivity patterns within DMN/SN/ANStructural MRI measures (regional cortical volumes/thickness, DTI metrics)Sleep spindle metrics and N2/N3 spectral characteristicsFluid biomarkers (CSF and plasma tau, Aβ40/42, Aβ42/Aβ40 ratio)

The cross-sectional arm will clarify which combinations of these features optimally discriminate hyperexcitability-positive from negative cases, and which best predict cognitive performance. The mechanistic arm will reveal which metrics track short-term fluctuations in excitability and cognition within individuals. Together, these findings can inform the design of composite scores or latent factors that may serve as more robust endpoints for future clinical trials (Toniolo et al., 2020).

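### The proposed biomarker panel is to discriminate hyperexcitability-positive from negative cases using, among its candidates, the EEG and fMRI measures that define that status

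*Protocol article*

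**What the plan says.** **The label.** Section 2.4.1 describes evidence of cortical hyperexcitability as "defined by at least one of: SEA on EEG above a predefined density threshold; or fMRI-defined hyperactivity in DMN/SN/AN". Section 2.6.1 carries this into the cross-sectional analysis, where "participants will be classified as hyperexcitability-positive vs negative", with a pointer back to 2.4.1.

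**How each component is set.** For EEG, section 2.3.4 states: "Participants will be labeled as EEG-positive or negative for SEA relative to HC normative values". Section 2.4.1 represents the normal limits as "upper tolerance limits (the 95th percentile) of spike density (events per hour) computed from the control group". For fMRI, section 2.3.3 states: "Hyperactivity will be defined as significantly elevated connectivity or activity within predefined network ROIs of DMN, SN, and AN relative to HC normative values".

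**The panel.** Section 3.3.1 lists five families of candidate features:
- spike incidence, density and spatial distribution from the 24-h and video-EEG recordings;
- fMRI hyperactivity indices and connectivity patterns in the default mode, salience and attention networks;
- structural MRI and DTI measures;
- sleep spindle and N2/N3 spectral measures;
- fluid biomarkers.

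It then says: "The cross-sectional arm will clarify which combinations of these features optimally discriminate hyperexcitability-positive from negative cases". The same sentence adds a second aim, finding the features that best predict cognitive performance.

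No section of the article removes the first two families from the predictors when the target is positive status, and none names a reference standard independent of them.

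**The concern.** The label is computed from the first two feature families, and the panel is then to be chosen for how well it recovers the label. A search over all five families will tend to return the definition. The resulting figure would not show whether structural MRI, DTI or plasma markers carry information about hyperexcitability, because a high value is expected either way.

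The panel matters outside section 3.3.1. The Abstract says it may support risk stratification and inform trial design, and the Conclusion repeats the expectation. Section 3.3.1 itself links the findings to composite scores that could serve as endpoints in later trials. A discrimination figure that follows from the definition is weak support for those uses.

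**Working it through.** The article states no AUC or other panel-performance figure, so there is nothing to reproduce. The check asks what discrimination would be found if no independent marker worked at all.

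**Inputs from the article.** The either/or label (2.4.1); the same label in the cross-sectional analysis (2.6.1); the candidate list and target (3.3.1); N = 300 (2.2.4).

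**Assumptions not in the article.** Spike density E and fMRI index F are each standard normal, with correlation 0 or 0.3. A fraction pE of participants exceeds the EEG cut-off cE and a fraction pF exceeds the fMRI cut-off cF, with values from 5% to 25%. Eight other biomarkers are pure noise.

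**Step 1: by logic.** The label is Y = 1 if E > cE or F > cF. The score max(E − cE, F − cF) is above zero for every positive and at or below zero for every negative, so its AUC is 1.00. The same holds for the two binary statuses: every positive has at least one status equal to 1 and every negative has both equal to 0.

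**Step 2: one defining measure alone.** Take E and F independent with pE = pF = 0.10.
- Share positive: 1 − 0.90 × 0.90 = 0.19.
- Share of positives who are EEG-positive: 0.10/0.19 = 0.526. All of these rank above every negative on E.
- The remaining 0.474 are positive through fMRI only. Their E is distributed as in the negatives, so they contribute 0.5.
- AUC of E alone: 0.526 + 0.474 × 0.5 = 0.76.

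**Step 3: fitted models by simulation.** Training N = 300, test N = 3,000, 200 replicates; AUC is taken in the test data. The additive model is a logistic regression on E, F and the eight noise markers.

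| pE, pF | Correlation | Share positive | Threshold rule | Additive model | Noise markers only |
|---|---|---|---|---|---|
| 0.15, 0.05 | 0 | 0.189 | 1.00 | 0.920 | 0.501 |
| 0.15, 0.05 | 0.3 | 0.184 | 1.00 | 0.954 | 0.499 |
| 0.10, 0.10 | 0 | 0.190 | 1.00 | 0.895 | 0.499 |
| 0.10, 0.10 | 0.3 | 0.179 | 1.00 | 0.937 | 0.499 |
| 0.15, 0.15 | 0 | 0.279 | 1.00 | 0.897 | 0.502 |
| 0.15, 0.15 | 0.3 | 0.257 | 1.00 | 0.937 | 0.500 |
| 0.25, 0.25 | 0 | 0.438 | 1.00 | 0.905 | 0.500 |
| 0.25, 0.25 | 0.3 | 0.408 | 1.00 | 0.939 | 0.499 |

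Logistic regression on the two binary statuses plus eight noise markers gave 1.00 (100 replicates).

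Section 2.2.4 offers one anchor for the share positive: "Assuming a conservative prevalence of approximately 15% across the clinical groups". It refers to the clinical groups only. Cutting both independent scores at the 92nd percentile gives 1 − 0.92 × 0.92 = 0.154 positive overall, and there a plain sum of the two scores has AUC 0.91.

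**Step 4: a weaker link between feature and label.** Suppose each feature comes from a separate measurement that correlates r with the one that set the label (pE = pF = 0.10, independent). The additive-model AUC is then 0.85 at r = 0.9, 0.77 at r = 0.7 and 0.68 at r = 0.5. It is lower, but still well above 0.50 with no working independent marker.

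**Step 5: which features exist in negatives.** Video-EEG and the described spindle analysis belong to the in-ward protocol (2.4.2), to which 2.4.1 invites participants with evidence of hyperexcitability. Features from that stay cannot contrast positives with negatives.

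**The case against.** The strongest reply is that section 3.3.1 is not an analysis rule. It sits among the implications for future research and speaks of a candidate panel. Section 2.6 contains no discrimination model, AUC or success criterion, and the panel is neither a primary nor a secondary outcome. Panel construction could be left to a fuller document. The part about status stands and limits the weight of the point. It does not remove it, because the article has not merely left a detail out: it states a candidate set and a target that overlap.

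Three stronger readings may tempt a reader, and the article does not support them.
- *The independent markers will never be assessed fairly.* Section 2.6.1 compares positives with negatives on structural, DTI and blood markers separately, with covariate-adjusted models and Holm–Bonferroni correction. Those comparisons are not affected by this point.
- *The panel will look near-perfect whatever model is used.* AUC 1.00 needs a threshold-type rule or the binary statuses as features. Additive models reach about 0.90 to 0.95, and a separate recording would give less. Section 2.4.1 also adjusts the EEG thresholds for age, sex and sleep state, so unadjusted density would separate slightly less cleanly than the adjusted score. The article sets no criterion by which the panel could be said to succeed.
- *The panel is meant to replace EEG and fMRI.* No section says so, and including core measures in a descriptive panel is not an error. The problem arises only when they predict a label that they define.

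**Conclusion.** The circularity is in the text. Followed as written, section 3.3.1 would yield a discrimination result fixed largely by the definition of positive status. With every other marker uninformative, AUC is 1.00 for a threshold rule or binary statuses, about 0.90 to 0.95 for an additive model, and 0.50 without the defining measures. The 1.00 follows from the definition, provided the features are on the scale used to set the label. The other figures rest on assumed normal scores, illustrative cut-offs and correlations of 0 or 0.3.

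The reach is limited to the biomarker-panel claim. A reader might infer that the primary incidence comparison or the secondary outcomes are circular for the same reason; nothing in this point shows that. The aim of predicting cognitive performance, in the same sentence of 3.3.1, is also sound, since cognitive scores are not part of the label.

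**What to change.** In section 3.3.1, and in the analysis plan if it covers the panel:

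1. State that any measure used to define a label is excluded from the predictors of that label.
2. Replace the combined target with two: predict EEG-positive status from non-EEG features, and fMRI-positive status from non-fMRI features. Structural MRI, DTI and plasma markers are candidates for both; the other modality may be added to each.
3. Use only features measured in both positives and negatives, which excludes those obtained only during the in-ward stay.
4. Report cross-validated AUC with a confidence interval.
5. Keep spike density and fMRI indices as candidates for outcomes outside the definition, such as cognitive scores.

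This needs wording and a restricted candidate list, and no new data. The cost is a lower reported AUC. Intervals may also widen, because neither single-modality label can have more positives than the combined one.

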#### Target identification for interventional studies

3.3.2

By relating SEA density and network hyperactivity to specific cognitive domains, network nodes, and sleep features, the study may highlight concrete targets for interventional modulation, such as:

Reducing nocturnal SEA in patients with MCI and early ADNormalizing DMN and salience network overactivity in ASD and ADHDEnhancing sleep spindle activity or stabilizing N2/N3 architecture in individuals with hyperexcitability-associated memory impairment

These targets can then be probed in controlled trials of anti-seizure medications (Vossel et al., 2021), neuromodulation approaches (e.g., TMS, tDCS) (Chai et al., 2019), or behavioral interventions that improve sleep quality and circadian regulation.

#### Design of precision medicine trials

3.3.3

The stratified, mechanistic data from LENDÜLET will support the design of precision trials by:

Identifying a subgroup of MCI patients with clear hyperexcitability-positive signatures and high risk of rapid progression, who might particularly benefit from early anti-hyperexcitability interventionsDefining EEG/fMRI-based inclusion criteria and surrogate endpoints for proof-of-concept studiesProviding quantitative benchmarks for expected changes in SEA density, network activity, and sleep measures that could be used to power future interventional trials

#### Methodological contributions and data sharing

3.3.4

The project’s standardized acquisition and preprocessing pipelines for EEG, MRI, and sleep data, together with open-source anonymized libraries planned for selected datasets, will facilitate methodological advancements, including:

Development and validation of automated SEA detection tools optimized for dementia and neurodevelopmental populationsTesting of advanced connectivity and graph-theoretical metrics to characterize hyperexcitability-related network reconfigurationExploration of multimodal clustering or latent variable models to delineate excitability-related endophenotypes that transcend traditional diagnostic boundaries

These resources may support future meta-analyses and collaborative efforts across centers, accelerating the translation of hyperexcitability research into clinical practice.

### Clinical implications

3.4

Although the present study is not interventional, its results may have several near- and medium-term implications for clinical practice.

